### Participant recruitment and timeline

Participants will be recruited via the home care provider organisations as depicted in the study flow diagram (see Fig. 1).

**Fig. 1 Fig1:**
[figure not shown]
TOMATO study flow diagram

The research team will provide training to the senior home care professionals on how to apply the eligibility criteria using the ‘Patients Association Nutrition Checklist’ [35] to identify potential participants at risk of malnutrition who will then be introduced to the researcher with their permission. Identified dyads will be informed about the research and asked by a senior home care professional if they would be happy to speak to a representative from the research team about taking part.

Identification and initial screening of potential participants living with dementia will be undertaken by a trained senior member of the direct care team from each participating home care provider. The person conducting the initial assessment will complete the screening form in line with the eligibility criteria. The researcher will also complete the form upon confirming eligibility and obtaining informed consent.

Home care professionals fulfilling the eligibility criteria will be identified and approached via a manager or senior member of staff from each participating home care provider. We will recruit additional home care professionals during the intervention to accommodate any loss to follow-up.

### Informed consent

All potential participants—people living with dementia and their family carer dyad, and home care professionals (triad)—will receive Participant Information Sheets (PIS), either directly from the researcher or through the home care provider. These will include a short one-page information leaflet with suitable visuals explaining the project and a consent form. The researcher will only contact eligible participants who have expressed interest and are willing to speak to them about taking part in the study. Trained researchers will explain the study to participants (using the PIS and consent form) and obtain written informed consent from those who volunteer and meet the eligibility criteria (see Table 1).

The researcher will make any formal decisions regarding capacity to consent to take part in the study. Formal assessment of capacity will be conducted by the researcher in accordance with the Mental Capacity Act (2005). If a person living with dementia lacks the capacity to consent, a personal consultee will be approached. A suitable personal consultee will be determined in consultation with the person living with dementia and the family member. If the personal consultee is willing, they will be asked to advise on the person's wishes regarding participation in the study. They will be provided with the consultee information sheet and consultee declaration form. Written informed consent will be obtained using the consultee declaration form.

Participants will have the option to complete the consent form either face-to-face (using the paper consent form) or electronically (eConsent). All participants will be informed that they are free to withdraw from the study at any stage without penalty.

### Sample size

As this is a feasibility study, a formal sample size calculation is not required. We will aim to recruit a purposive sample across a diverse range of participants including socio-demographic, carer relationship and living arrangements, dementia severity and length of dementia caring/working experience. The target sample size is 32 participant dyads (person with dementia and carer) from across the participating home care providers, with the aim of achieving 25 dyads at the 4-month follow-up. This accounts for approximately 20% dropout and provides a 95% exact binomial confidence interval for retention, assuming 32 dyads are enrolled and 80% retained, from 64% to 93%. These align with sample size recommendations and is consistent with those typically indicated for feasibility studies [42].

We will train enough staff to deliver the intervention to ensure that recruited dyads will have at least 75% of their home care visits conducted by trained home care professionals. The number of trained staff will be based on usual working patterns, such as shift patterns, consistency of allocation to people receiving support, agency size, and working logistics, with an anticipated range of 20 to 40 staff per organisation. Table 2 outlines the schedule of enrolment, intervention and assessment.

**Table 2 Tab2:**
[figure not shown]
TOMATO project schedule of enrolment, intervention and assessment

### About the adapted nutritional intervention

The tailored nutrition intervention is based on the key principles of the person-centred nutritional care model (see Additional file 3: TOMATO logic model). The nutrition intervention targets home care professionals by delivering nutrition awareness training and providing them with adapted resources. These resources demonstrate various practical ways, including behavioural and environmental aspects, to take action and support people living with dementia at home with eating and drinking.

The intervention will be delivered by trained home care professionals in the homes of the participating dyads over a 4-month period.

#### Home care professional’s training session (face to face and online)

The nutrition awareness training session for home care professionals will be delivered face-to-face or online. Online sessions will be delivered either on individuals’ own devices or via the participating home care organisation’s online platform, depending on preference. The training incorporates presentations using PowerPoint slides and group discussions.

The training covers awareness raising about person-centred nutritional care, how to spot nutritional decline, availability of food and drinks, monitoring and care planning, working together with family carers and friends, enhancing the mealtime experience at home and engaging in activities, ensuring consistency of care and sourcing evidence-based information. This will ensure all staff possess the required knowledge to identify people at nutritional risk and to implement nutritional care plans. The training is expected to last approximately 2 h and will feature case scenarios and group discussions.

Upon completion of the nutritional care awareness level training, all staff will receive a certificate of completion as part of their continuing professional development (CPD). The training session will be conducted by an expert nutritionist-dietitian and trained research team facilitators. Home care professionals who cannot attend the training on the day will have the opportunity to attend a separate session. Table 3 shows details of the intervention, the COM-B components and highlights the training session’s main content and delivery mode.

**Table 3 Tab3:** Component of the nutrition intervention

Component of the nutrition intervention					
Intervention component and delivery mode	Objectives	Training session *content*		Behaviour Change Wheel (BCW) Intervention Functions	Associated Behaviour Change Techniques (BCTs)
		Topics covered	Key principles		
1.Training session (online and face to face) 2. Guidebook on eating and drinking well at home with dementia, provided in a comprehensive and handy guide format for easy access and reference	1. To raise awareness about nutrition (eating and drinking) for people living with dementia at home 2. To ensure home care professionals have the required knowledge about spotting people at risk of undernutrition and actions to take in response 3. To ensure home care professionals have access to evidence-based information booklet (detailed and handy guide) on eating and drinking well with dementia at home	Availability of food and drinks	How to accommodate for changes in appetite, food preferences and ability with practical suggestions for modifying food, planning menus and improving the presentation of food	Education	5.1. Information about health consequences 5.3 Information about social and environmental consequences 7.1 Prompts/cues 9.1. Credible source
		Monitoring and care planning	Spotting the signs of poor nutrition and using validated tools to identify people likely to be at risk of undernutrition	Training	4.1. Instruction on how to perform the behaviour 6.1 Demonstration of the behaviour
		Relationship: Working together	Practical ways of working together with family members and close friends to improve food and drink intake	Enablement	1.2 Problem solving 1.3. Goal setting (outcome) 1.4 Action planning 7.1 Prompts and cues 12.5 Adding objects to the environment
		The mealtime experience at home and activities	Improving the dining environment and mealtime experience practical activities to stimulate appetite, evoke memories and create a sense of purpose	Environmental restructuring	12.1. Restructuring the physical environment 12.2. Restructuring the social environment 12.5. Adding objects to the environment
		Consistency of care	Improved communication between all those involved with care and the provision and prioritisation of nutrition and hydration	Modelling	6.1 Demonstration of the behaviour
		Provision of trusted information	Access to trusted information, training, resources and current guidelines		

#### Resources: eating and drinking well with dementia at home guide

The adapted guides contain detailed information on person-centred nutritional care domains, consistent with the content of the nutrition awareness training. All participating family carers, friends, and home care professionals will receive both the detailed guidebook and a ‘handy’ guide titled Eating and Drinking Well at Home with Dementia, which offers simple approaches and tools to support the nutritional care of people living with dementia. The handy guide, a small-sized booklet, is designed for easy access and reference (see Fig. 2).

**Fig. 2 Fig2:**
[figure not shown]
Eating and drinking well with dementia at home resources to be used during the intervention testing

#### Additional support

A trained member of the research team and facilitator will contact participating home care professionals via telephone or email to provide additional support and encourage monthly reflection, including the documentation of an action log on the intervention throughout the 4-month intervention period. Peer support will be promoted among trained participating home care professionals, with peer discussions focusing on addressing any challenges faced, as well as on person-centred nutrition care topics covered during the nutrition awareness training and in the resources.

### Outcome measures and data collection

The primary outcome will be an assessment of study feasibility, including acceptability, recruitment and retention, protocol adherence and adaptations, compliance with study procedures including completion of questionnaires, percentage withdrawal, completion of outcomes and assessments, barriers and enablers to intervention delivery. We will relate the evaluation to focused components of feasibility studies [43]. This includes the assessment of acceptability, demand, implementation, practicality, adaptation, integration, and expansion. Secondary outcomes will be collected at baseline and 4-month after the first visit by the home care professional, unless recorded as routine data, at other time intervals. In such cases, all data recorded over the intervention period will be gathered. They will include nutritional status of the person with dementia (body weight, height to calculate Body Mass Index, BMI of < 20 kg/m^2^ as an indicator of undernutrition), quality of life using EQ-5D-5L/EQ-5D-5L-Proxy and DEMQoL/DEMQoL-Proxy [44–46] (as a robustness check and interview administered) and functional status (Deterioration in Daily Living Activities in Dementia) [47] and carer burden using Zarit Burden Interview [48]. Outcome measures were selected based on our logic model and informed by consultation with the PPI and Project Management Group. Table 4 outlines these assessments and strategies for measuring the outcomes of the TOMATO study.

**Table 4 Tab4:** TOMATO outcome measures

Feasibility parameter	How they will be assessed?		When the measures will be collected? [pre- only, post- only, pre and post intervention]
Recruitment rate	Percentage of participants recruited from participating home care provider		Pre and post
Attrition rate	Percentage of participants who drop out of the study before completion		Pre and post
Intervention Adherence	Percentage of staff who adhere to the intervention schedule (including the completion of the monthly action logs for 4 months)		Post-only
Components of focus			
Acceptability	Semi-structured interviews/focus group with participants		Post-only
Demand	Analysis of screening data Semi-structured interviews/focus group with participants		Post-only
Implementation	Documentary analysis Semi-structured interviews/focus group with participants		Post-only
Practicality	Semi-structured interviews/focus group with participants		Post-only
Adaption	Documentary analysis Semi-structured interviews/focus group with participants		Post-only
Integration	Documentary analysis Semi-structured interviews/focus group with participants		Post-only
Expansion	Documentary analysis Semi-structured interviews/focus group with participants		Post-only
Assessment	Outcome measures	Description	
Participants living with dementia			
Nutritional status Weight-related health risks	Body Mass Index (BMI)	Body weight (kg) and height (m^2^) will be combined to determine BMI (weight (kg)/height (m^2^)). BMI of < 20 kg/m^2^ will be an indicator of undernutrition	Pre and post
Health-related quality of life (HRQoL)	Dementia Quality of Life questionnaire (DEMQoL) and DEMQoL-Proxy	4 level scale across 28 items (DEMQoL) or 31 items (DEMQoL-Proxy) with higher scores indicating better quality of life	Pre and post
	EuroQol 5-Dimension 5-Level (EQ-5D-5L) and EQ-5D-5L-Proxy	The descriptive system assesses health-related quality of life across five domains using a 1–5 level scale, where levels range from 1 (indicating no problems) to 5 (indicating extreme problems). The visual analog scale (VAS) measures quality of life on a scale of 0 to 100, with higher scores indicating better quality of life	Pre and post
Functional status	Deterioration in Daily Living Activities in Dementia) using Modified Barthel Index measures	2-point scale rating with 0 to 20 points. Higher score indicates greater independence	Pre and post
	Functioning status using Lawton-Brody Instrumental Activities of Daily Living Scale	4-point scale. Higher scores indicate greater independence and better functional ability	Pre and post
Carers			
Carer burden	Carer burden using Zarit Burden Interview	0 to 88 points; higher scores indicate severe burden	Pre and post
Data associated with costs of intervention	Data collected via a proxy resource utilisation questionnaire informed by existing questionnaires such as Resource Utilisation in Dementia (RUD-Lite)	This will be assessed via participants’ case report form and discussion with the researcher including utilisation of primary and secondary healthcare services usage and informal carer time	Post-only

### Nested process evaluation

As part of the study process evaluation, qualitative data will be generated from semi-structured interviews or focus groups conducted by the researcher at 4 months.

A sample of participants receiving home care and their carers (*n* = 12 dyads) will be invited to participate in semi-structured interviews. Family carers will be given the option to have a separate interview, and paid care for the person with dementia will be offered.

Home care professionals (*n* = 12), and home care managers (*n* = 4) will be invited to take part in an interview or a focus group (in pairs of 2–3 staff per provider organisation). We will adopt blended approaches, incorporating a combination of face-to-face interviews (using a Dictaphone) and online interviews/focus groups (via Zoom/Teams software), which will be video and/or audio-recorded and transcribed verbatim.

We will use a pre-designed topic guide, developed in conjunction with our PPI group consisting of key open-ended questions. Participants will be asked to feed back about various aspects of their experiences to inform a potential future trail including receiving or delivering the nutrition intervention, identifying priority areas, the delivery process, how the approach worked, the barriers, facilitators, and aspects that could be improved. For all participants, we will collect demographic data from home care records, including age range, gender, ethnicity, living arrangements, and dementia diagnosis.

Documentary analysis will be undertaken from a review of care plans of people with dementia (at baseline; during preceding 4-month period and at 4 months) using a checklist of key data, e.g. food and drink intake, weight recording, costs.

A bespoke document will be used to collect data on intervention fidelity and dose. This document will be completed by home care professionals, informal carers, or healthcare professionals, or via standardised recording in care plans. Implementation fidelity will be guided by a revised version of Carroll et al.’s conceptual framework [49].

### Feasibility economic component

To estimate the associated costs, data will be collected on the use of health and social care services and support provided by family carers and friends, using a questionnaire adapted from and informed by existing tools such as the Resource Utilisation in Dementia-Lite Version (RUD-Lite) [50]. Data will be gathered from home care records, family carer dyads, and home care professionals.

Specifically, family carers will be asked about the number of hours they spend providing informal care. Data collected on resource use will relate to accessing healthcare, including hospital admissions, ambulance call-outs, length of hospital stay, personal social services, prescription data, and oral nutrition supplements.

This resource use will be costed as per conventional practice via the use of administrative data sets such as NHS Reference Costs, Personal Social Services Research Unit (PSSRU) Costs of Health and Social Care, and the NHSBSA Drug Tariff. Where relevant, missing cost and health-related quality of life data will be estimated using multiple imputation. Levels of missing data per cost category will also be reported.

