### Data analysis

#### Quantitative

We will conduct quantitative data analysis primarily using descriptive statistics, including frequencies, means, and percentages with 95% confidence intervals (CIs) (using SPSS v26.0). Categorical data will be presented as frequencies and percentages.

Specifically, we will describe participants’ demographic characteristics and outcome scores collected at baseline and at 4 months using suitable summary statistics. We will also report the proportion of missing data for each outcome measure. We will calculate the differences between baseline and 4-month follow-up, with 95% CIs, for all outcome scores listed in Table 4. We will assess and estimate key progression indicators (using the traffic light system as in Table 5) and obtain stakeholder input to support interpretation of findings and decisions regarding proceeding to a larger trial [52]. These indicators will include recruitment rates, the proportion of homecare staff adhering to the intervention schedule (defined as setting at least four actions over the 4-month intervention period, documented in the monthly action logs), and the proportion of participating clients for whom the outcome measure questionnaire booklet was completed.

We will analyse resource use data collected during the final 1-month follow-up period. Cost will be estimated based on the most recent PSSRU Unit Costs of Health and Social Care [53], and the NHS Drug Tariff for medication costs [54]. Where the specific type of medication is uncertain, we will apply an average cost across all plausible options.

A CONSORT flow diagram will present the flow of participants through the study [37]. The number of participants approached, eligible, consented and enrolled and retained at follow-up will be reported along with reasons for withdrawal or dropout where possible. We will summarise and report rates and patterns of missing questionnaire data to inform the selection of outcomes and administration strategy for a full trial. A statistical analysis plan will be developed and reviewed by the Chief Investigator and Project Management Group prior to commencing analysis.

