### Safety reporting

Considering the adverse effects of malnutrition for people living with dementia, the intervention has low risk, as it will help to spot the signs of poor nutrition and provide support for those in receipt of care by staff from the participating home care provider. No serious adverse events (SAEs) are anticipated from participating in this study, although older people living with dementia would be expected to have a higher rate of intercurrent illnesses, such as infections impacting on attrition or falls leading to hospitalisation. We will report adverse events (AEs) and loss to follow-up, monitor for capacity to consent with deteriorating health, and continue to follow up where possible.

To determine the safety of the intervention, all AEs and SAEs and their possible relation to the intervention will be carefully monitored and documented, with classification as either unrelated or related to the intervention. Home care professionals will be trained to document AEs and report back to the research team within a set period of time. All AEs will be followed up until it has been determined that the study intervention is not the cause, and the event has been resolved or a decision has been made for no further follow-up.

The research team will notify the sponsor (BU) within 24 h of any SAEs that are related to the intervention. The Health Research Authority Research ethics committee will be notified within 15 days of the chief investigator becoming aware of the SAE using the non-CTIMP safety report to REC form.

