## Discussion

This study will determine the feasibility of our nutrition intervention to improve nutritional care for people with dementia receiving home care, which will inform the development and implementation of a future pilot RCT, should this be feasible. The feasibility study will measure resource use, identify key drivers of associated costs, and provide preliminary information for a future trial. This will be balanced against the costs of hospitalisation and the need for NHS resources associated with adverse events. Through the research, feasibility and acceptability data will be provided to understand the barriers and enablers for implementation. This knowledge will help guide implementation to facilitate greater uptake, adoption and spread into policy and practice in a future study.

Home care professionals are uniquely positioned to play a significant role in supporting people living with dementia. While previous RCTs [24, 25] have shown positive effects on quality of life and delayed nutritional decline through nurse- or multidisciplinary team-delivered nutrition interventions for older adults at home, evidence on interventions delivered specifically by home care professionals remains limited. The TOMATO study will address this gap and contribute valuable insights into the context-specific challenges faced by home care professionals in delivering nutritional care to people living with dementia who are in receipt of home care.

This study has potential far-reaching implications, as identifying nutrition-related health risks and intervening at an early stage for people with dementia living at home can help reduce deterioration in mental and physical health and wellbeing. As such this means there is increased potential for improved quality of life, maintenance of independence, reduced burden for family and home carers and increased likelihood of remaining at home for as long as possible. The study will produce new outputs, including new data, training and toolkit materials and as a feasibility study will be tested to improve the nutritional care of people with dementia living at home and receiving home care.

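### Dyads who leave before 4 months have no resource-use questionnaire, so imputing their costs from dyads who stayed would probably understate health-care cost

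*Protocol article*

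**What the plan says.** Table 4 (Outcome measures and data collection) has a cost row based on a proxy resource-use questionnaire, "including utilisation of primary and secondary healthcare services usage and informal carer time". Its timing is post-intervention only, whereas every other participant and carer measure in that part of the table is taken before and after.

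Under Data analysis (Quantitative) the plan states: "We will analyse resource use data collected during the final 1-month follow-up period". Under Feasibility economic component, the remedy for gaps is: "Where relevant, missing cost and health-related quality of life data will be estimated using multiple imputation". The same section lists admissions, ambulance calls and length of stay among the cost items. It names home care records and home care professionals as data sources besides the dyads, and promises to report missingness for each cost category.

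The Sample size section plans 32 dyads "with the aim of achieving 25 dyads at the 4-month follow-up". Safety reporting expects more intercurrent illness in this population, "such as infections impacting on attrition or falls leading to hospitalisation". The Discussion says the study will identify the main drivers of cost and adds: "This will be balanced against the costs of hospitalisation and the need for NHS resources associated with adverse events".

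**The concern.** By the protocol's own account, illness is one reason for leaving, and hospital use is one of the main things being costed. Missingness may therefore depend on the quantity that is missing. A dyad that leaves early has neither a baseline nor a follow-up questionnaire, so an imputation model has little of that dyad's own cost history to work with and borrows from dyads who reached 4 months.

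Collecting cost and resource-use data is a stated secondary objective. If hospital use is under-observed in those most likely to incur it, the study may misjudge which items drive cost, and a future trial would inherit that error when it designs its economic component. An analysis plan written later can refine the imputation model, but it cannot recover data that were never collected.

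**Working it through.** **1. The plan's own retention figures.** The stated 95% exact interval for retention, with 32 enrolled and 80% retained, is 64% to 93%. Since 80% of 32 is 25.6, a whole number of dyads is needed. The Clopper-Pearson interval for 26/32 (81.3%) is 63.6% to 92.8%, which reproduces the stated figure. For the follow-up target of 25/32 (78.1%) it is 60.0% to 90.7%. The planned loss is therefore 32 − 26 = 6 or 32 − 25 = 7 dyads, that is 19% to 22%.

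**2. What a leaver contributes, source by source.**
- Questionnaire (Table 4): nothing, because it is given only at 4 months.
- Home care records and staff (Feasibility economic component): some use before exit. They are not stated to continue once the care package ends, and are an uncertain source for length of hospital stay.
- Care-plan review (Nested process evaluation): a baseline, a preceding 4-month period and 4 months, with costs on the checklist. This is again partial.
- Routine data over the intervention period (Outcome measures and data collection): this sentence concerns secondary outcomes, and the list that follows does not include resource use.
- Adverse event records (Safety reporting): these may show that an admission happened. The section does not say that resource use is recorded at exit.
- Final-month analysis: a dyad that leaves in months 1 to 3 contributes nothing to that window even if earlier records exist.

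**3. Size of the effect.** The documents give no costs, so this is an illustration. Let m be the number of the 32 dyads who leave for health reasons, k the assumed ratio of their cost to the stayers' mean, and f = m/32. Other leavers are assumed to cost the same as stayers, and imputation is assumed to return the stayers' mean.

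True mean ÷ stayers' mean = (1 − f) + f × k

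Understatement = 1 − 1 / [(1 − f) + f × k]

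| m | k | True mean ÷ stayers' mean | Understatement |
|---|---|---|---|
| any | 1 | 1.000 | 0% |
| 2 | 2 | 30/32 + 2 × 2/32 = 1.063 | 5.9% |
| 6 | 2 | 26/32 + 6 × 2/32 = 1.188 | 15.8% |
| 6 | 3 | 26/32 + 6 × 3/32 = 1.375 | 27.3% |
| 7 | 2 | 25/32 + 7 × 2/32 = 1.219 | 17.9% |
| 7 | 3 | 25/32 + 7 × 3/32 = 1.438 | 30.4% |

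To the extent that records supply a leaver's use, that dyad drops out of m and the bias shrinks towards zero.

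**4. Quality of life.** EQ-5D-5L and DEMQoL, with proxy versions, are taken at baseline, so imputation can condition on the leaver's own value. If a score were imputed after a death, an assumed EQ-5D value of 0.4 to 0.7 in place of 0 would raise the 32-dyad mean by 0.4/32 = 0.013 to 0.7/32 = 0.022 per death.

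**5. The time window.** The secondary objective is cost and resource use while the intervention is delivered, which is 4 months. A final-month analysis covers 1/4 = 25% of that period, for stayers as well as leavers. If the sentence instead describes only when the data are gathered, the recall period is not stated. The two places need reconciling on either reading.

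**The case against.** The strongest reply is that resource use is not drawn from the questionnaire alone. Records, staff and care plans are further sources, follow-up continues where possible, and missing data by cost category and reasons for dropout will be reported. This stands in part. A reader might infer that nothing is known about leavers' resource use, and the documents do not support that. They do not show complete cover of hospital use either.

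Second, the imputation model and the handling of death belong in the statistical analysis plan, which the protocol says will be written before analysis, and the imputation sentence is qualified. This also stands. A reader might infer that the plan commits to imputing costs or quality of life for people who have died. It does not say so; it only fails to rule it out. Nor are death and care-home admission named as expected reasons for loss, and people at end of life or permanently cared for in bed are excluded. What an analysis plan cannot settle is whether exit data are collected.

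Third, much larger figures are tempting. If stayers averaged 0.5 hospital days and all seven leavers 2 days, the mean would be (25 × 0.5 + 7 × 2)/32 = 0.83, and 0.5 would be 40% too low. At 5 days the mean would be 1.48 and the shortfall 66%. Those results come from ratios of 4 and 10 applied to every leaver, for which the documents offer no basis. Safety reporting links illness to attrition but does not say that most exits will have that cause.

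**Conclusion.** The point holds for health-care cost. Early leavers have no questionnaire data, other sources may cover their hospital use only partly and only to exit, and imputing from stayers would probably bias cost downwards. With 7 of 32 missing, the understatement is about 6% if two leave for health reasons at twice the stayers' cost, and about 18% to 30% if all seven cost two to three times as much. There is none if leavers cost the same or records supply their use. These figures rest on assumed ratios and on an imputation that carries no information about why a dyad left.

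The argument is weaker for quality of life, because baseline values exist. The consequence is limited: there is no between-group cost comparison, cost is not among the Table 5 progression criteria, and the Discussion calls the information preliminary. The change is worth making because it is cheap and serves a stated objective.

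**What to change.** 1. First reconcile the final-month window under Data analysis with the secondary objective, which covers the whole delivery period. Then use one recall window for leavers and stayers alike, or express cost per unit of observed time for both. Otherwise a start-to-exit record for leavers and a one-month record for stayers would be mixed in one mean, which could introduce a new bias.
2. When a dyad leaves, and if the carer agrees, complete the existing resource-use questionnaire and extract home care records up to the exit date. Record the date and reason.
3. State that neither costs nor quality of life are imputed after death, and report observed-data results beside the imputed ones.

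The cost is one extra use of an existing form for an expected 6 to 7 dyads, some record extraction, and a few sentences of text. The drawback is a short additional contact with a carer at what may be a difficult time. Some carers will decline, so the gap will be reduced but not closed.
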